# Randomized phase II trial of MRI-guided salvage radiotherapy for prostate cancer in 4 weeks versus 2 weeks (SHORTER)

**DOI:** 10.1186/s12885-023-11278-3

**Published:** 2023-08-22

**Keywords:** Prostate cancer, Salvage radiotherapy, Stereotactic body radiotherapy (SBRT), MR-Linac, MRI-guided radiotherapy (MRgRT), Genitourinary, Hypofractionation, Ultra-hypofractionated, Toxicity

## Abstract

**Background:**

Ultra-hypofractionated image-guided stereotactic body radiotherapy (SBRT) is increasingly used for definitive treatment of localized prostate cancer. Magnetic resonance imaging-guided radiotherapy (MRgRT) facilitates improved visualization, real-time tracking of targets and/or organs-at-risk (OAR), and capacity for adaptive planning which may translate to improved targeting and reduced toxicity to surrounding tissues. Given promising results from NRG-GU003 comparing conventional and moderate hypofractionation in the post-operative setting, there is growing interest in exploring ultra-hypofractionated post-operative regimens. It remains unclear whether this can be done safely and whether MRgRT may help mitigate potential toxicity. SHORTER (NCT04422132) is a phase II randomized trial prospectively evaluating whether salvage MRgRT delivered in 5 fractions versus 20 fractions is non-inferior with respect to gastrointestinal (GI) and genitourinary (GU) toxicities at 2-years post-treatment.

**Methods:**

A total of 136 patients will be randomized in a 1:1 ratio to salvage MRgRT in 5 fractions or 20 fractions using permuted block randomization. Patients will be stratified according to baseline Expanded Prostate Cancer Index Composite (EPIC) bowel and urinary domain scores as well as nodal treatment and androgen deprivation therapy (ADT). Patients undergoing 5 fractions will receive a total of 32.5 Gy over 2 weeks and patients undergoing 20 fractions will receive a total of 55 Gy over 4 weeks, with or without nodal coverage (25.5 Gy over 2 weeks and 42 Gy over 4 weeks) and ADT as per the investigator’s discretion. The co-primary endpoints are change scores in the bowel and the urinary domains of the EPIC. The change scores will reflect the 2-year score minus the pre-treatment (baseline) score. The secondary endpoints include safety endpoints, including change in GI and GU symptoms at 3, 6, 12 and 60 months from completion of treatment, and efficacy endpoints, including time to progression, prostate cancer specific survival and overall survival.

**Discussion:**

The SHORTER trial is the first randomized phase II trial comparing toxicity of ultra-hypofractionated and hypofractionated MRgRT in the salvage setting. The primary hypothesis is that salvage MRgRT delivered in 5 fractions will not significantly increase GI and GU toxicities when compared to salvage MRgRT delivered in 20 fractions.

**Trial registration:**

ClinicalTrials.gov Identifier: NCT04422132. Date of registration: June 9, 2020.

**Supplementary Information:**

The online version contains supplementary material available at 10.1186/s12885-023-11278-3.

## Background

Prostate cancer is the most common non-cutaneous cancer and the second leading cause of cancer death in men [1]. It is predicted that the number of prostate cancer cases will almost double by the year 2030 [2]. For men with localized prostate cancer, radical prostatectomy is a common definitive treatment modality [3]. After radical prostatectomy, approximately one-third to one-half of men with high-risk features will develop biochemical recurrence (BCR) [4–7].

Post-operative radiotherapy is the current standard of care for men who develop BCR or are at risk of BCR after radical prostatectomy. Post-operative radiotherapy is a potentially curative treatment after prostatectomy for men with BCR and may avoid or delay the need for chronic, non-curative treatment, such as long-term androgen suppression. Given the increase in both prostate cancer diagnosis and the proportion of men with high-risk disease undergoing radical prostatectomy, the number of men requiring post-operative radiotherapy is likely to increase [8]. As such, optimizing radiotherapy approaches for post-operative management is an important and unanswered question. Minimizing genitourinary (GU) and gastrointestinal (GI) toxicity and maximizing quality of life are critical for men with a high chance of cure and long life-expectancy following salvage treatment [9].

Adjuvant radiotherapy, the administration of immediate post-operative radiotherapy based on adverse pathological features, has been demonstrated to improve biochemical progression free survival (PFS) across multiple prospective randomized trials [10–12]. More recently, early salvage post-operative radiotherapy has become an accepted paradigm. In this approach, men delay post-operative intervention until the time of BCR or if there is a persistently elevated serum prostate-specific antigen (PSA) level after prostatectomy. In support of this paradigm shift, three recent randomized controlled trials and the harmonized ARTISTIC meta-analysis have demonstrated that adjuvant radiotherapy, as compared with salvage radiotherapy, does not improve event-free survival [4, 5, 7, 13]. Additionally, the salvage approach may also avoid overtreatment in the subset of men that despite high-risk features do not develop BCR. The aforementioned studies have helped clarify the timing of post-operative intervention, however, integration of genomic classifiers, optimal target volumes (including pelvic nodal coverage), and the use and duration of androgen suppression therapy remain controversial. Additional studies are needed to further refine patient selection and improve post-operative management.

Increasingly, there has been a trend toward delivering higher doses of radiation over fewer treatment sessions, termed hypofractionation, as opposed to longer courses of treatment with conventional fractionation (1.8–2 Gy/fraction) [14–16]. Further, as prostate cancer is believed to have a low α/β ratio relative to other tumor types, the therapeutic ratio may favor hypofractionation over conventional regimens [17–20]. The preliminary report of the phase III randomized NRG-GU003 study demonstrated that moderately hypofractionated post-operative radiotherapy (62.5 Gy in 25 fractions) does not increase patient-reported GU or GI toxicity over conventional post-operative radiotherapy (66.6 Gy in 37 fractions). At a median of 24 months, change in mean GU and GI scores in the moderate hypofractionation arm and conventional fractionation arm were neither clinically nor statistically significant (mean GU = -5.2 vs mean GU = -0.3, p= 0.81; mean GI = -2.2 vs mean GI = -1.5, *p* = 0.12). Therefore, moderate hypofractionation is non-inferior to conventional fractionation for post-operative RT in measures of late toxicity [21]. This finding is significant, as hypofractionation provides patients with shorter and more accessible courses of radiotherapy, thereby reducing treatment burden. 

The advent of magnetic resonance imaging (MRI)-guided radiotherapy (MRgRT) – enabled through the integration of MRI and linear accelerator (MR-LINAC) technology may facilitate safe delivery of hypofractionated and ultra-hypofractionated regimens. Multi-parametric MR imaging on the MR-LINAC improves target delineation and this feature combined with real-time MR image-guidance and tracking, allows for reduction in planning margins and accounts for inter-fractional changes in anatomy during treatment thereby decreasing dose to adjacent structures, including the bladder and rectum [22]. In addition, the MR-LINAC technology can facilitate online adaptive planning as needed. Taken together, MRgRT may safely allow larger radiation doses to be delivered in fewer fractions in the intact and post-operative setting. The MIRAGE phase III study comparing MRI-guidance versus standard computed tomography (CT)-guidance with stereotactic body radiotherapy (SBRT) for intact prostate cancer demonstrated that acute grade ≥ 2 GU toxicity was significantly reduced among men receiving MRgRT (43.4.1% vs. 24.4%, *p* = 0.01). Acute grade ≥ 2 GI toxicity was also significantly reduced in men receiving MRgRT (10.5% vs. 0%, *p* = 0.003) [23]. Similarly, the SCIMITAR phase II study evaluated the safety profile of post-prostatectomy SBRT and incorporated a pre-planned, non-randomized exploratory analysis of toxicity and patient-reported quality-of-life (QoL) outcomes between MRI-guidance versus CT-guidance. Compared with CT-guided post-operative SBRT, MRgRT was associated with significantly lower rates of any-grade acute GI toxicity (41.9% vs. 72.5%, *p* = 0.0056) per CTCAE version 4.0 criteria, corresponding to an estimated absolute reduction of 30.5%. In terms of late effects, MRgRT was associated with numerically lower any-grade late GI toxicity, however, these differences were not significantly different (37.7% vs. 29%, *p* = 0.4) when compared with CT-guidance. There were no differences in acute or late GU toxicity in the comparison of patients treated with CT versus MRI-guided SBRT. Overall, three patients experienced grade 3 toxicity (GU, *n* = 1; GI *n* = 2), notably no patients treated with MRgRT experienced any grade 3 toxicity or grade ≥ 2 GI toxicity. While additional randomized studies are needed, these findings demonstrate the potential of MRgRT to improve the precision and safety of post-operative radiation delivery [24].

The SHORTER trial (NCT04422132) is designed to evaluate if MR-guided ultra-hypofractionated post-operative radiotherapy (5 fractions in two weeks) has a non-inferior GU and GI toxicity profile as compared with MR-guided moderately-hypofractionated post-operative radiotherapy (20 fractions in four weeks) among prostate cancer patients undergoing salvage radiotherapy. This randomized phase II study lays the foundation to potentially redefine the standard of care for post-prostatectomy patients with BCR to include MRgRT and decrease treatment burden.

## Methods/design

### Objectives

The primary objective is to demonstrate that 5 fractions of ultra-hypofractionated MRgRT does not significantly increase patient-reported GI and GU symptoms as compared with 20 days of hypofractionated MRgRT at 2 years after treatment completion.

#### Primary endpoint

The co-primary endpoints are change scores in the bowel (GI) or urinary (GU) domains of the Expanded Prostate Cancer Index Composite (EPIC). The change scores will reflect the 2-year score minus the pre-treatment (baseline) score.

#### Secondary endpoints

1. Compare patient-reported GI symptoms using the EPIC questionnaire at the end of RT and 3, 6, 12, and 60 months from end of treatment.2. Compare patient-reported GU symptoms using the EPIC questionnaire at the end of RT and 3, 6, 12, and 60 months from end of treatment.3. Compare time to progression (TTP) where progression is defined as the first occurrence of biochemical failure (BF), local failure, regional failure, distant metastasis (DM), institution of new unplanned anticancer treatment, or death from prostate cancer (PCSM).4. Compare freedom from biochemical failure (FFBF) and TTP rates with an alternate PSA ≥ PSA nadir + 2 ng/mL definition of BF.5. Compare local failure, regional failure, salvage therapy (*i.e.,* institution of new unplanned anticancer treatment), DM, PCSM, and overall survival (OS) rates.

#### Inclusion criteria

Men aged ≥ 18 with histologically confirmed prostate cancer after prostatectomy with detectable PSA. Patients with detectable post-prostatectomy PSA whether (1) persistently detectable post-operatively or (2) developing biochemical recurrence after prostatectomy (initially undetectable) are eligible. Patients with early BCR or persistently detectable PSA after prostatectomy must wait a minimum of 6 months post-prostatectomy but can initiate ADT as indicated. PSA does not need to be detectable for men with pathologically node positive disease.KPS ≥ 70Patient with no evidence of distant metastatic disease on positron emission tomography (PET)/CT/MRI or bone scan < 90–180 days prior to enrollment. Patients with positive pelvic lymph nodes are eligible.Ability to receive MRI-guided radiotherapyEquivocal evidence of metastatic disease outside the pelvis on standard imaging requires documented negative biopsyAbility to complete the EPIC questionnaire

#### Exclusion criteria

Prior history of receiving pelvic radiotherapyPatients with inflammatory bowel diseasePatients with a prior or concurrent malignancy whose natural history or treatment has the potential to interfere with the safety or efficacy assessment of ultra-hypofractionated radiotherapyHistory of bladder neck or urethral disease

### Evaluation of randomization and blinding

This study will employ a randomized phase II non-inferiority design to compare 5 fractions of ultra-fractionated MRgRT versus 20 fractions of moderately hypofractionated MRgRT in the salvage setting for prostate cancer patients after prostatectomy. Patients will be stratified according to baseline EPIC bowel and urinary domain scores (*i.e.,* high bowel score and high urinary score vs. high bowel score and low urinary score vs low bowel score and high urinary score vs. low bowel score and low urinary score) as well as pelvic radiotherapy and androgen therapy (*i.e.,* yes vs. no), for these factors are expected to be associated with the primary outcome. Within each strata, patients will be randomized 1:1 to receive 5 fractions or 20 fractions using permuted block randomization. The trial schema is displayed in Fig. 1.

**Fig. 1 Fig1:**
[figure not shown]
Trial Schema. Expanded Prostate Cancer Index Composite (EPIC), EuroQol-5D index (EQ-5D) and International Prostate Symptom Score (IPSS) quality of life (QoL) surveys are collected at baseline, end of salvage radiotherapy, and at 3 month, 6 month, 12 month and 60 month follow up. GI, gastrointestinal; GU, genitourinary; RT, salvage radiotherapy. *EPIC score groups defined as: high bowel score > 96, low bowel score ≤ 96, high urinary score > 84, low urinary score ≤ 84. **Patients with PSA > 0.4 ng/mL, high-risk Decipher genomic classifier scores, or pathologically node positive disease will receive pelvic nodal radiotherapy and androgen deprivation therapy (ADT) as per the clinician’s discretion

### Interventions

#### Radiation treatment planning

After consent and eligibility verification, patients will undergo CT/MRI simulation for radiotherapy planning. Patients will receive delivery of either 32.5 Gy in 5 fractions over 2 weeks or 55 Gy in 20 fractions over 4 weeks to the prostate fossa ± pelvic lymph nodes. Indications for nodal coverage include PSA > 0.4 ng/ml, high Decipher score, or pathologically positive lymph nodes as per the clinician’s discretion [25–27]. For patients requiring nodal coverage, those on the 5 fraction arm will receive 25.5 Gy to the pelvic lymph nodes and those on the 20 fraction arm will receive of 42 Gy to the pelvic lymph nodes. Patients randomized to the 5 fraction arm cannot be treated on consecutive days. Patients undergo salvage radiotherapy no earlier than 6 months post-prostatectomy. The radiotherapy prescription doses for the 20 fraction and 5 fraction schedules are provided in Table 1.

**Table 1 Tab1:** Radiotherapy Prescription Doses to Prostatic Fossa and Pelvic Lymph Nodes for 20 fraction and 5 fraction schedules

Organ	Dose (Gy)	BED (Gy)	$${\mathbf{E}\mathbf{Q}\mathbf{D}}_{2}$$	Dose (Gy)	BED (Gy)	$${\mathbf{E}\mathbf{Q}\mathbf{D}}_{2}$$	Dose (Gy)	BED (Gy)	$${\mathbf{E}\mathbf{Q}\mathbf{D}}_{2}$$
**PROSTATIC FOSSA**									
**Comparison of 1.8 Gy × 37 (66.6 Gy) vs. 2.75 Gy × 20 (55 Gy) vs. 6.5 Gy × 5 (32.5 Gy)**									
Prostate (α/β = 2.7)	66.6 (1.8 Gy × 37)	111	64	55 (2.75 Gy × 20)	111	64	32.5 (6.5 Gy × 5)	111	64
Bladder (α/β = 3)	66.6 (1.8 Gy × 37)	107	64	55 (2.75 Gy × 20)	105	63	32.5 (6.5 Gy × 5)	103	62
Rectum (α/β = 5)	66.6 (1.8 Gy × 37)	91	65	55 (2.75 Gy × 20)	85	61	32.5 (6.5 Gy × 5)	75	53
**PELVIC LYMPH NODES**									
**Comparison of 1.8 Gy × 25 (45 Gy) vs. 5.1 Gy × 20 (42 Gy) vs. 5.1 Gy × 5 (25.5 Gy)**									
Prostate (α/β = 2.7)	45 (1.8 Gy × 25)	75	43	42 (2.1 Gy × 20)	75	43	25.5 (5.1 Gy × 20)	74	42

##### Contour

All contouring will be done as per RTOG consensus recommendations for the prostate bed and normal pelvic structures [28]. The planning target volume (PTV) expansion for the CTV will be 2-3 mm depending on physician discretion. The bladder should not be included in the CTV (bladder overlap may be removed from the CTV via Boolean function).

##### Treatment dose planning parameters for 32.5 Gy in 5 fractions

The planning target volume (PTV) will receive the prescribed dose of 32.5 Gy in 5 fractions. The volume of PTV receiving the prescription dose (VPrescription Dose) of 32.5 Gy should be ≥ 95% and not exceed 110% (hotspot) (see treatment dose planning parameters listed in Additional File 1)*.*

##### Treatment dose planning parameters for 55 Gy in 20 fractions

The planning target volume (PTV) will receive the prescribed dose of 55 Gy in 20 fractions. The volume of PTV receiving the prescription dose (VPrescription Dose) of 55 Gy should be ≥ 95% and not exceed 115% (hotspot) (see treatment dose planning parameters listed in Additional File 1)*.*

##### Adaptive planning for 5 fraction arm

Adaptive planning will be permitted for the 5 fraction arm.Prior to treatment, each patient will undergo an MRI scan.2D shifts will be performed to align relevant anatomy (bladder wall, rectum, prostatic fossa).Simulation contours will be rigidly copied to the patient's MRI scan. If delineation changes, the scan will be recontoured.Predicted dose algorithm will determine if treatment dose parameters meet planning dose parameters.Patients will undergo adaptive planning if the treatment dose parameters do not meet the planning parameters and per the protocol planning parameters as outlined (see Additional File 1).

##### General concomitant medication and supportive care guidelines

Androgen deprivation therapy (ADT) and pelvic nodal irradiation will be administered for patients with PSA > 0.4 ng/ml, high Decipher score (> 0.6), or pathologically positive lymph nodes [25–27]. ADT should consist of a luteinizing hormone-releasing hormone (LHRH) agonist or antagonist and be initiated prior to and within 6 months of starting radiotherapy and not exceed 24 months in duration.

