##### Analysis of secondary endpoints:

Secondary safety endpoints: Between treatment arms differences in each safety endpoints measured as change in domain specific EPIC scores at a specific time points (*i.e.,* end of RT, 3, 6, 12, 24, and 60 months) from base line will be evaluated using t-test or Wilcoxon rank sum test whichever is more appropriate. The domain specific EPIC scores measured over time will also be modeled using a linear mixed effects model with fixed effects including time points, treatment arm, Gleason score, baseline PSA, T-stage, age, race, and a random intercept. Between treatment arms differences in GI and GU EPIC scores at 2 years adjusting for baseline scores and other covariates will be assessed using analysis of covariance (ANCOVA). Results from the primary unadjusted analysis and covariates adjusted analysis are expected to lead to similar conclusions. Otherwise, further investigation concerning possible heterogeneous subgroup effects and/or the impacts of missing values will be carried out to ensure that meaningful conclusions can be made.Secondary efficacy endpoints: For competing-risk endpoints such as PCSM, local failure (LF), regional failure (RF), TTP, and DM, Gray’s cumulative incidence method will be used with death as a competing risk for LF, RF and DM and death not due to prostate cancer for PCSM and TTP. OS and FFBF will be estimated by the Kaplan–Meier method and compared between arms with the log-rank test. Cox regression will be used to obtain hazard ratios (HRs) for OS and TTP. Fine and Gray’s regression will be used for the endpoints with competing risks. Adjusted HRs and the respective 95% confidence interval will be computed. Baseline PSA, stratification variables (baseline EPIC score and ADT status), age, race, and other covariates (Gleason, T-stage), will be adjusted for as appropriate in this analysis.

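### The article gives conflicting rules on whether pelvic nodal radiotherapy and ADT are required or discretionary, does not define how they are stratified, and omits nodal radiotherapy from the stratification variables in the analysis

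*Protocol article*

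**What the plan says.** **Whether the treatments are required.** Four places in the article address this.

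- The section on concomitant medication and supportive care gives this rule: "Androgen deprivation therapy (ADT) and pelvic nodal irradiation will be administered for patients with PSA > 0.4 ng/ml, high Decipher score (> 0.6". The third criterion is positive nodes on pathology. Discretion is not mentioned.
- Abstract, Methods: nodal coverage is optional, "and ADT as per the investigator’s discretion".
- Radiation treatment planning: "Indications for nodal coverage include PSA > 0.4 ng/ml, high Decipher score, or pathologically positive lymph nodes as per the clinician’s discretion". This sentence concerns nodal coverage only.
- Fig. 1 legend: patients meeting the same criteria "will receive pelvic nodal radiotherapy and androgen deprivation therapy (ADT) as per the clinician", and the sentence ends by leaving this to discretion.

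**How they are stratified.** The section on randomization and blinding crosses the baseline EPIC bowel and urinary groups into four written-out levels. It then adds a further stratification "as well as pelvic radiotherapy and androgen therapy (*i.e.,* yes vs. no), for these factors are expected to be associated with the primary outcome". The Abstract names nodal treatment and ADT without levels.

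**How they are analysed.** For the efficacy regressions, the section on secondary endpoints adjusts as appropriate for the "stratification variables (baseline EPIC score and ADT status" pair and other covariates. The fixed effects listed for the mixed model of EPIC scores are time, arm, Gleason score, baseline PSA, T-stage, age and race. The ANCOVA at 2 years adjusts for baseline scores and covariates that are not named.

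**The concern.** The first problem is practical. A site treating a patient who meets one of the three criteria cannot tell from the article whether leaving out nodal irradiation or ADT follows the protocol or departs from it.

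The second concerns the design. If nodal radiotherapy and ADT form one joint yes/no factor, a patient planned for only one of them has no clear level. Discretionary use makes such patients possible. If they are two factors, the list of stratification variables in the analysis section leaves one out. The text therefore needs work on either reading.

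The article itself expects these factors to be associated with the primary outcome. The mixed model nevertheless lists neither, and the efficacy adjustment names only ADT. At stake are clear instructions to sites, analyses that match the randomization, and readable evidence that the arms were comparable on treatments likely to affect bowel and urinary scores.

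**Working it through.** **1. The treatment statements side by side**

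| Place | Nodal radiotherapy | ADT |
|---|---|---|
| Concomitant medication section | given if any criterion is met | given if any criterion is met |
| Abstract, Methods | discretionary | discretionary |
| Radiation treatment planning | criteria listed, discretionary | not addressed |
| Fig. 1 legend | to be given, yet discretionary | to be given, yet discretionary |

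The first row cannot be squared with the second, or with the third for nodal radiotherapy. The fourth contains both ideas. The inclusion criteria also allow ADT to begin during the post-prostatectomy wait, and the article does not say which PSA measurement the 0.4 ng/mL criterion refers to.

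**2. The stratification on its two readings**

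Baseline EPIC gives 4 levels, and 136 patients are randomized.

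- One joint yes/no factor: 4 × 2 = 8 strata, mean 136/8 = 17 patients. A patient planned for one treatment only has no evident level.
- Two yes/no factors: 4 × 2 × 2 = 16 strata, mean 136/16 = 8.5 patients. Every patient has a stratum, but the analysis section's list then omits nodal radiotherapy.

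**3. The plan's own power figures**

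Inputs from Sample size and accrual: 61 evaluable per arm, one-sided α = 0.05, margins of 6 (GI) and 5 (GU), SDs of 13.2 and 10.5. The true difference is taken as 0.

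- Standard error = SD × √(2/61): GI 13.2 × 0.1811 = 2.39; GU 10.5 × 0.1811 = 1.90.
- Noncentrality = margin/SE: GI 6/2.39 = 2.51; GU 5/1.90 = 2.63.
- Noncentral t with 120 degrees of freedom: power 80.3% (GI) and 83.4% (GU). The plan states 80% and 83%.
- 122/0.90 = 135.6, rounded up to 136, as stated.

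The sample size is reproduced, and nothing in this point changes it.

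**4. Illustration of what an imbalance could do**

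The documents give neither an imbalance between arms nor an effect of nodal radiotherapy or ADT on EPIC, so both are assumed here.

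Shift = difference in use between arms × effect in EPIC points. Differences of 10 to 30 percentage points with effects of 3 to 8 points give shifts from 0.10 × 3 = 0.3 to 0.30 × 8 = 2.4 points. A 20-point difference with a 5-point effect gives 0.20 × 5 = 1 point.

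Power uses noncentrality (margin − shift)/SE when the shift goes against the 5-fraction arm. Type I error at the margin uses shift/SE when the shift favours it.

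| Shift (points) | GI type I error | GU type I error | GI power | GU power |
|---|---|---|---|---|
| 0 | 5.0% | 5.0% | 80.3% | 83.4% |
| 0.5 | 7.5% | 8.3% | 74.0% | 76.1% |
| 1 | 11.0% | 13.1% | 66.8% | 67.3% |
| 2 | 20.8% | 27.5% | 50.8% | 47.0% |

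**The case against.** Four replies have force.

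- **Timing of the decision.** A reader might infer that clinicians can choose nodal radiotherapy and ADT once they know the arm. The documents do not support this. Patients are randomized in permuted blocks within strata, so planned status has to be declared before assignment. Table 2 also places PSA and the 22-gene test at screening. What remains is narrower. The article does not use the term open-label, but whoever delivers 5 or 20 fractions knows the arm, and a later departure from the declared plan could differ by arm.
- **Patients without a stratum.** A reader might infer that some patients cannot be stratified at all. That holds only if there is one joint factor, and even then patients not receiving both treatments could be counted as no. Two binary factors is an equally natural reading, because the article speaks of factors in the plural and the Abstract names two treatments. The sound criticism is ambiguity.
- **Size.** The shifts in the table are assumptions. With declared status balanced by stratified blocks, a large imbalance would require many departures from plan. The illustration runs in both directions and does not show that bias is likely.
- **Condensed article.** Registration fields and the handling of departures may well be in the full protocol. Their absence here is not counted against the plan. That reply does not cover statements that conflict within the article, or a list of stratification variables that omits one the article names elsewhere.

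**Conclusion.** The point stands as one of consistency and definition. The concomitant medication section conflicts with the Abstract and the planning section, and sits awkwardly with the Fig. 1 legend. This review takes no position on which rule should apply. The stratification wording does not settle whether there is one factor or two. The analysis section omits nodal radiotherapy from the stratification variables, and its mixed model lists neither treatment, although the article expects both to be associated with the primary outcome.

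No error in the sample size or power is involved. The documents do not establish that the primary comparison is biased. The figures of about 11% for GI type I error and about 67% for GI power show only how sensitive the comparison is to a 1-point shift, under an imbalance and an effect that are both assumed. Correction is worthwhile because it affects what sites do and costs little.

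**What to change.** 1. Reconcile the Abstract, the Fig. 1 legend, the planning section and the concomitant medication section into one statement of whether nodal radiotherapy and ADT are required or discretionary. State which PSA measurement the criterion refers to. The choice is for the trial's clinical leadership.
2. Define the stratification explicitly, either as two binary factors or as one factor with every combination assigned to a listed level. Base it on the status declared before randomization.
3. Correct the list of stratification variables in the secondary analysis section. Include the declared nodal radiotherapy and ADT values in the ANCOVA, the mixed model and the efficacy regressions.
4. Optionally, tabulate departures from the declared plan by arm.

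The cost is wording and a few model terms. The total stays at 136 and no procedures are added. The drawback is sparser strata if two binary factors are used: 16 with a mean of 8.5 patients, against 8 with a mean of 17. If that is a concern, a single factor with some levels merged is an alternative.
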